# ULB-Hopital Erasme*, and Department of Statistics, ULB-School of Public Health**, Bruxelles

# and AZ StJan***, Brugge

## Sponsors:

## Federal Public Service Public Health, Food Safety and Environment, Belgium.

## Cepheid, Europe.

## Introduction

Methicillin-resistant *Staphylococcus aureus* (MRSA) strains have become endemic pathogens in acute and chronic healthcare facilities in Belgium and are also spreading in the community. MRSA infection is causing increased public concern as it carries a significant risk of morbidity, mortality and has been linked to substantial excess healthcare costs (1). The increased risk of prolonged hospital stay and fatal outcome from bloodstream or surgical infection with MRSA, as compared with no infection or infection with methicillin-susceptible *S.aureus*, has been well documented (1).

Efficient control of MRSA transmission within healthcare facilities critically depends on screening for and isolation of MRSA carriers among admitted patients. Active surveillance cultures for MRSA are now part of clinical practice recommendations both in Europe and the USA (2-3). Indeed, studies have indicated that up to 70 % of the patient reservoir for MRSA among hospitalized patients can only be detected by active sampling and selective cultures of muco-cutaneous colonization sites, including the nares, throat, skin, wounds, rectum and insertion sites for invasive devices. MRSA colonization places the individual patient at increased risk of healthcare associated infection and constitutes a reservoir for transmission to other hospitalized patients. There is an urgent public health need for early and reliable detection of carriers of MRSA among patients admitted to healthcare facilities, to inform patient isolation and decontamination procedures, and thereby more effectively control cross-infection (4).

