**Secondary aims:**

To compare the following secondary outcomes during periods of MRSA carrier screening among hospital admissions by means of rapid PCR testing versus conventional culture:

1. Median time required for detection of MRSA carriage after admission
2. Median time required for starting isolation of MRSA carriers
3. Number of patient-days of MRSA carrier stay in non-isolated conditions
4. MRSA nosocomial infection rate
5. MRSA cross-transmission rate
6. Sensitivity and specificity of PCR vs conventional MRSA screening

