**Intervention study design**

The study will be a **cluster randomized intervention trial,** with **cross-over design** carried out in three phases:

(1) a 3 month screening reinforcement phase during which the adherence to the admission and discharge MRSA screening protocols will be promoted and monitored monthly to achieve > 80 % compliance rate, application of isolation precautions to MRSA colonized patients will be measured and checked to achieve > 80 % compliance and the MRSA acquisition rate will be checked to lie within 95 % confidence limits of the projected 3% estimate. In addition, the length of stay per ward will be measured and checked for homogeneous distributions.

(2) a 5 month conventional detection test (standard care) phase during which MRSA screening will be performed by optimized conventional culture methods 6 days a week during working hours.

(3) a 5 month rapid detection test intervention phase during which admission MRSA screening will be performed by rapid PCR testing 7 days a week during working hours.

After eligible wards in each hospital have been checked to meet these inclusion criteria in phase (1), the sequential order of inclusion of eligible study wards in phase (2) and (3) will be randomly assigned within each centre by assigning a number to each ward and using a computer generated list of random numbers per study arm in each hospital so that one half of the wards will start phase (2) for the first 5 months and then phase (3) for the following 5 months whereas the other study wards will be “crossed-over” to follow the reverse sequence. No wash-out period will be used between phase (2) and (3). If the analysis of patient length of stay by ward indicates homogeneous distribution with markedly different median values between wards, stratified randomisation of wards within short/long (below/above pooled median) stay groups will be considered.

The planned study start date is: November 3rd, 2008 for the baseline observation and completion is planned on December 31st, 2009 (post-poned to end January, 2010 see addendum).

Admission screening: evaluation of patient sampling procedures:

During the entire study period (baseline and intervention phase), the infection control nurse responsible for the study will perform daily rounds in each of the study wards to ensure that screening of all newly admitted patients is being done systematically and without delay.

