To monitor MRSA acquisition for primary endpoint measurement, active discharge surveillance will be performed in all patients who have stayed in study wards for more than 48 h by collecting surveillance cultures for MRSA either on the day of being discharged or within 72 h prior to discharge from the study ward. Discharge surveillance sampling will be performed by the study protocol nurse on daily ward rounds during week days, by collecting swabs of nares, throat, perineum, and any wound, bladder or intravenous catheter exit site and endotracheal aspirate in ventilated patients for conventional selective MRSA culture (see appendix 1). For the denominator, a patient will be counted as two ward admissions if staying outside the ward for more than 24 h.

All isolates will be saved at -80°C for typing of relevant isolates to identify transmission clusters. Genotyping will be performed by *spa* sequence analysis and SCC*mec* typing (see appendix 5 for MRSA typing procedure).

Interim analysis and contingency plan.

After the first 10 weeks of the 3-month baseline period, 2 weeks will be used to analyse data and check ward eligibility based on fulfillment of the following “pass criteria”:

(1) > 80 % compliance with admission and discharge conventional culture screening, calculated for weeks 8-10 for the pooled admissions to all study wards;

(2) > 80 % compliance with additional MRSA contact isolation procedures, calculated for weeks 8-10 based on a sample of observations of 50 patient care contacts per hospital in all study wards;

(3) pooled incidence of nosocomial MRSA acquisition ≥ 3 new cases /100 at risk admissions in the study wards for weeks 1-10.

These criteria must be met for each hospital to ensure sufficient compliance with the protocol, a sufficient denominator of exposed number of patients per month in the study wards and target incidence figures. If either of these pass criteria is not fulfilled, the two trial phases can be extended to 6 or 7 months and/or further compliance reinforcement will be undertaken before starting the randomisation of units for inclusion in the intervention phase.

In addition, MRSA isolates will be typed to ensure that no atypical SCC*mec* variants are emerging.

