**Secondary endpoints**

These will include three related process of care indicators:

1. Time (h) between admission and notification of MRSA positive culture/PCR
2. Time (h) between admission and placement of newly detected MRSA carrier in contact isolation

Secondary endpoints will also include the following microbiologically-documented outcomes:

1. Number of patient-days of MRSA positive patients cared for with standard precautions and not isolated
2. Cumulative incidence of MRSA nosocomial colonisation, defined as number of new cases of hospital-acquired MRSA (first positive culture >48 h after admission) divided by the number of admitted patients who stayed ≥ 3 days and were MRSA negative on admission by culture and PCR testing, if performed.
3. Cumulative incidence of MRSA nosocomial infection, defined as number of new cases of hospital acquired MRSA infection (according to CDC definitions for nosocomial infection and with first MRSA positive culture > 48 h after admission) divided by number of admitted patients who stayed ≥ 3 days.
4. Number of clusters of ≥ 2 cases/unit of acquired MRSA colonisation with a clonally related strain, defined as a MRSA strain with the same spa type or PFGE major type.
5. Sensitivity and specificity of rapid PCR test compared to conventional culture for MRSA screening, taking into account one parallel set of admission nasal screening samples per patient.

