# Two-Center Intervention Study to Evaluate the Impact of Rapid Molecular Screening on Nosocomial Transmission of Methicillin-Resistant *Staphylococcus aureus* (MRSA).

# Addendum 1 to the protocol – modification of analysis plan (February 7th, 2009)

Based on the results of the base-line period (November 3rd, 2008 –January 15th, 2009), 7 wards of Erasme hospital and 6 wards of AZ St Jan hospital have been randomized and allocated either to the intervention or control arm for the first 5 month study period to begin on February 9th, 2009. Stratified randomization of wards was performed according to the hospital and average patients’ length of hospital stay.

In the base-line period, the compliance rates with key processes of care were achieved (admission screening cultures and infection control precautions > 80%) or closely approached (discharge screening cultures 68% and improving during the baseline weeks). However, the incidence of MRSA nosocomial acquisition was lower than hypothesized in the protocol: 0.79% (95%CI: 0.34% - 1.55%). This incidence rate was unexpectedly low compared to previously recorded rates. When considering the higher limit of the 95%CI, the planned sample size allows detection of a 50% reduction in incidence of nosocomial acquisition with 80% power and taking into account a potential cluster effect only if the pooled incidence in both hospitals combined is analysed as the primary endpoint. Therefore, although heterogeneity between the two hospitals will be studied as planned, the pooled results for both hospitals will be presented and analysed as the primary endpoint.

An additional interim analysis is planned three months after the beginning of the study to obtain a new estimate of the incidence of MRSA nosocomial acquisition in the control units and to check if the number of subjects is large enough to reach the objectives.

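### The cluster endpoint links acquired cases in a ward by shared type alone, with no limit on time or overlap of stay, and its typing criteria do not match the typing that is planned.

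*Protocol*

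**What the plan says.** Secondary aim 5 of the protocol is the "MRSA cross-transmission rate". The endpoint that serves it through strain typing is item 4 of the microbiologically documented outcomes under Secondary endpoints: "Number of clusters of ≥ 2 cases/unit of acquired MRSA colonisation with a clonally related strain", with clonal relatedness "defined as a MRSA strain with the same spa type or PFGE major type".

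Under Intervention study design, the paragraphs on case finding say that isolates are stored for "typing of relevant isolates to identify transmission clusters", and that "Genotyping will be performed by *spa* sequence analysis and SCC*mec* typing". Appendix 5 describes spa sequencing only. The Introduction says that MRSA "strains have become endemic pathogens in acute and chronic healthcare facilities in Belgium".

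Each compared period is a 5-month phase (for the control condition, "a 5 month conventional detection test (standard care) phase"). Addendum 1 records that "7 wards of Erasme hospital and 6 wards of AZ St Jan hospital have been randomized", 13 wards in all.

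**The concern.** A cluster of transmission normally needs two elements: strains that cannot be told apart, and an opportunity for one patient's strain to reach the other. The definition asks only for the first. A case in the first week of a phase and another in the last week, in the same ward and with the same spa type, count as a cluster even if no stay connects them. Where MRSA is endemic, separate introductions of the same type are plausible, so a shared type within a ward-phase is weak evidence of spread.

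The typing criteria also do not fit the laboratory plan. One of the two permitted criteria, PFGE major type, has no planned data behind it. One planned measurement, SCCmec type, has no role in the definition.

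What is at stake is the meaning of the count. This is the only listed endpoint that uses strain identity to address cross-transmission. As written, it mixes linked cases with coincidental matches in unknown proportion.

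**Working it through.** **Text check.** The Secondary aims, the Intervention study design section, the endpoint and analysis sections, both addenda and Appendix 5 were read for any condition on cluster membership. The only stated bound is the same unit. A second bound, the same 5-month phase, is implied because the arms are compared by phase. No maximum interval, overlap of stay or other epidemiological link appears. PFGE occurs only in the endpoint definition.

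**Data available.** Ward admission date and time are recorded, and lengths of stay are needed for the patient-days denominator of the primary endpoint. A time or overlap rule therefore needs no new data.

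**Illustration.** The plan gives no figure for this endpoint, so there is none to reproduce.

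*Spacing of unrelated cases.* For two independent dates, uniform over T = 150 days (5 months), P(gap > w) = (1 − w/T)².
- w = 14: (1 − 14/150)² = 0.82
- w = 30: (1 − 30/150)² = 0.64
- w = 60: (1 − 60/150)² = 0.36

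*Chance clusters under the written rule.* Inputs from the protocol: 1,850 control patients per hospital (3,700 in all), baseline incidence 0.79% (Addendum 1) and 13 wards. Expected cases per ward-phase: m = 3,700 × 0.0079 / 13 = 29.2 / 13 = 2.25.

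Assumed, not in the documents: cases are independent and Poisson, with no transmission. The commonest type has a share of 25% to 60%, and the rest is split evenly over 5 to 10 types.

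For a type with share f, P(at least 2 cases in a ward-phase) = 1 − exp(−mf)(1 + mf). This is summed over types and multiplied by 13.
- Low end (25%, ten other types of 7.5%): mf = 0.562 gives 0.110. The others have mf = 0.169, giving 0.0127 each and 0.127 together. Total 0.237 × 13 = 3.1.
- High end (60%, five other types of 8%): mf = 1.349 gives 0.390. The others have mf = 0.180, giving 0.0144 each and 0.072 together. Total 0.462 × 13 = 6.0.

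*With a time link.* The model was simulated with uniform dates, joining consecutive same-type cases in a ward only if they are within w days. Case dates stand in for stays here, since stay lengths are not given.

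| Rule | Chance clusters, control arm, 13 wards |
| --- | --- |
| Type only, as written | about 3 to 6 |
| 30-day link | about 1.3 to 3.3 |
| 14-day link | about 0.6 to 1.9 |

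(The low end for 14 days is 0.66 in simulation.) A window removes roughly half or more of the chance matches, but not all of them.

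**The case against.** A reader might go further and infer that the rule exaggerates the benefit of PCR, because chance matches rise faster than case numbers when cases are few. The documents do not support that as a criticism of the missing window. In the same model, halving cases from the 0.79% rate lowers the cluster count by 62-72% under the written rule and by 70-76% with a window, so a window does not cure that scaling. At the planned 3% versus 1.5% the fall under the written rule is 40-64%. With a dominant type it is smaller than the 50% fall in cases. The rule can also undercount, since separate episodes of one type in a ward-phase merge into one. At the planned control rate (50/6.5 = 7.7 cases per ward-phase) with a 70% type, the mean is 1.19 clusters with no limit, against 1.31 (14 days) and 1.40 (30 days). The direction of error is not uniform, and no claim of bias towards either arm is made.

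Nor does the PFGE alternative show that linking is looser in practice. If PFGE is not done, no PFGE match can arise. It is a mismatch to reconcile.

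Other objections have weight:
- Same-type cases far apart are not necessarily unrelated. A persistent ward source or an unsampled carrier could connect them. This is why the type-only count should be kept as a sensitivity analysis.
- The type distribution is not in the documents, so the counts show what the rule permits and are not a forecast.
- The listed analyses (A, C, D and E) assign no test to the cluster count, so no efficacy conclusion hangs on it.
- An analysis plan that is not shown could add a window. The protocol, however, does not leave the definition open. It states one, and states it without a time or contact condition.

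**Conclusion.** The point holds as a matter of definition. Shared type within a ward is sufficient, cases up to a 5-month phase apart qualify, and the typing named in the endpoint differs from the typing planned. Under the assumptions above (no transmission, independent cases at uniform dates, the assumed type shares), about 3-6 control-arm clusters would arise by chance at the baseline rate, and a time link would cut that to about 1.3-3.3 (30 days) or 0.6-1.9 (14 days). How many coincidental matches the trial would contain cannot be known from the documents. The primary endpoint does not use the cluster definition, so this is a minor correction to a secondary endpoint.

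**What to change.** Redefine item 4 as at least two acquired cases in the same unit and study period, with the same spa type and the same SCCmec type, whose ward stays overlap or are separated by no more than a gap fixed before the data are seen. Delete the PFGE alternative. Report the count under the type-only rule as a sensitivity analysis, and apply both rules identically in the two arms.

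The cost is about one sentence in the endpoint definition and one extra tabulation. Stay dates and both typing results are already to be collected. The drawback is that links through an unsampled carrier or a persistent ward source may be missed; the sensitivity count shows how far the result depends on the chosen gap.

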## Study design

**Study type and patient population**

The study will be an open label, **cluster randomized intervention trial,** with **cross-over design.** It will be carried out in parallel over a one year period in two large hospitals in

1. patients admitted to high risk surgical, medical and geriatric wards of Erasme hospital (7 to 8 wards)
2. patients admitted to the intensive care departments, medical and geriatric wards of AZ St Jan hospital (6 to 7 ward).

The Erasme hospital is an 858-beds academic hospital located in Brussels, including medical and surgical care departments. The AZ-St Jan hospital is an 800-bed general teaching hospital located in Brugge, including medical and surgical care departments. Both institutions have an integrated MRSA surveillance and control program in place for over 10 years. These programs adhere to the national recommendations for MRSA control in acute care hospitals (BICS-CSH/HGR 2003). These include: active screening of MRSA carriers on admission by selective culture of nasal, throat and wound sites in high risk patients and/or units, flagging of previously detected MRSA carrier patients at re-admission, placement of MRSA carriers in single room with contact isolation precautions and decolonisation therapy of carriers with nasal mupirocin and antiseptic bathing for 5 days.

The choice of a minimum size of effect of 50% reduction in MRSA acquisition is based on the assumption that a 6-fold reduction of transmission rate can be expected from placing MRSA positive patients in isolation, and that the reduction from 3 to 0 days of unisolated stay can be expected by the intervention. Assuming a baseline rate of 3% nosocomial acquisition rate in the exposed population of study wards, the study population will include 3,700 patients in each hospital with approximately 50 new cases of MRSA acquisition in the control arm (n= 1,850 patients) versus 25 new cases in the intervention arm (n= 1,850 patients).

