**Study endpoints and statistical analysis**

The **primary endpoint** of the study will be the following microbiologically documented outcome:

1. **Incidence density rate of MRSA nosocomial colonisation**, defined as the number of new cases of hospital-acquired MRSA (first positive culture > 48 h after admission) divided by the number of patient days at risk (defined as cumulated lengths of stay by patients who stayed ≥ 3 days and were MRSA negative on admission screening by conventional culture, and, if performed, PCR test).

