The **primary analysis** will be based on Poisson regression two level model (individual patient and unit exposure) performed at each hospital level to assess the impact of the intervention on local incidence-density of MRSA nosocomial colonisation, and ajusted for four potentially confounding factors. The dependent variable will be endpoint 1 above. The ward level **independent variables** will include (1) **intervention arm**, (2) MRSA **colonisation pressure** (as determined by monthly proportion of MRSA colonisation-days/total patient-days among patients admitted during the preceding month in one particular ward), (3) **staff** **compliance with standard and isolation precautions** (as determined by a sample of 50 observations per ward/ trial period, including 25 care opportunities for patients under MRSA isolation precautions and 25 for patients cared for with standard precautions; see appendix 6 for precautions compliance monitoring procedure) (4) **antibiotic use** (as determined by cumulated number of Defined Daily Doses of J01 ATC class of antimicrobial drugs per monthly period) and (5) monthly bed occupancy rate.

Heterogeneity of effect by ward/hospital will be assessed. **To quantify the protective efficacy of the intervention** for the at risk population per centre, the adjusted Rate Ratio (and 95% confidence interval) of nosocomial MRSA acquisition will be calculated for the intervention arm in all study wards per hospital. Pooled analysis of average effect for both hospitals will be calculated. In case of significant heterogeneity between hospitals, hospital level will be added as covariate in the model.

**Secondary analyses** will include:

A. Logistic regression two level models (individual patient and unit exposure) will be performed at each hospital level to assess the impact of the intervention on local cumulated incidence of MRSA nosocomial colonisation. The dependent variable will be endpoint 6 above. The **independent variables** will include patient age, sex and the 5 independent ward level indicators as described above for the primary Poisson analysis.

Heterogeneity of effect by ward/hospital will be assessed. Pooled analysis of average effect for both hospitals will be calculated. In case of significant heterogeneity between hospitals, hospital level will be added as covariate in the model.

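### Antibiotic use enters the primary model as a raw monthly DDD total, which mixes antibiotic intensity with ward size and occupancy; it should be a rate per patient-days

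*Protocol*

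**What the plan says.** The primary analysis, described under Study endpoints and statistical analysis, is a "Poisson regression two level model (individual patient and unit exposure) performed at each hospital level". Addendum 1 makes the pooled result for both hospitals primary, after "7 wards of Erasme hospital and 6 wards of AZ St Jan hospital have been randomized".

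The dependent variable is new hospital-acquired cases "divided by the number of patient days at risk". The ward-level covariates besides the intervention arm are:

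- colonisation pressure, the "monthly proportion of MRSA colonisation-days/total patient-days among patients admitted during the preceding month in one particular ward";
- staff compliance, which Annex 6 defines as a ratio over observed situations;
- antibiotic use, the "cumulated number of Defined Daily Doses of J01 ATC class of antimicrobial drugs per monthly period";
- bed occupancy, given as "5) monthly bed occupancy rate".

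Secondary analysis A, the logistic model for cumulative incidence, takes over the same five ward-level indicators, so the antibiotic definition carries into it. No denominator for the DDD total appears anywhere in the protocol.

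**The concern.** Antibiotic use is the only numeric ward covariate left as a volume. The confounder of interest is antibiotic selection pressure on the patients in a ward, which is consumption relative to patient-days. A monthly total also rises with the number of beds and with how full they are.

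The wards are of mixed type. The protocol allows any adult ward, and at one site the study population is "patients admitted to the intensive care departments, medical and geriatric wards of AZ St Jan hospital". Such wards can differ in size and in prescribing at once, so two wards with quite different antibiotic exposure per patient-day can get the same value, and one ward can get different values in two months with the same prescribing. At stake is how well the primary and secondary models adjust for antibiotic exposure, and whether the fitted antibiotic coefficient can be interpreted.

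**Working it through.** The protocol states no figure for this covariate, so there is none to reproduce. The check rests on an identity:

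monthly DDD total = beds × occupancy × days × DDD per patient-day.

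Only the last factor, the DDD density, is exposure intensity. The protocol gives no ward bed numbers, occupancy or DDD data, so all ward figures below are assumptions, with a 30-day month.

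**1. Size.** At 80% occupancy and 60 DDD per 100 patient-days:
- 15 beds: 15 × 0.80 × 30 = 360 patient-days; 360 × 0.60 = 216 DDD.
- 30 beds: 30 × 0.80 × 30 = 720 patient-days; 720 × 0.60 = 432 DDD.

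The covariate doubles at identical exposure per patient-day. Per 100 patient-days both wards score 60.

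**2. Masked difference.** A 20-bed ward at 80% occupancy and density 90: 20 × 0.80 × 30 = 480 patient-days; 480 × 0.90 = 432 DDD. This equals the 30-bed ward at density 60, so a 50% difference in exposure does not show.

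**3. Occupancy.** For 30 beds at density 60:
- 60% occupancy: 540 × 0.60 = 324 DDD.
- 90% occupancy: 810 × 0.60 = 486 DDD.

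The covariate rises by 50% (486/324 = 1.5) with no change in prescribing per patient-day.

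**4. How much of the total is antibiotic intensity?** On the log scale the factors add. If they are independent, each contributes a variance of ln(1 + CV²). The assumed CVs are 15% to 40% for beds, 5% to 15% for occupancy and 15% to 50% for density. Month length is ignored.

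| Case | CV beds | CV occupancy | CV density | Share of density |
| --- | --- | --- | --- | --- |
| All ward-months, lowest | 40% | 15% | 15% | 0.0223 / (0.1484 + 0.0223 + 0.0223) = 12% |
| All ward-months, highest | 15% | 5% | 50% | 0.2231 / (0.0223 + 0.0025 + 0.2231) = 90% |
| Within a ward, lowest | fixed | 15% | 15% | 0.0223 / (0.0223 + 0.0223) = 50% |
| Within a ward, highest | fixed | 5% | 50% | 0.2231 / (0.0025 + 0.2231) = 99% |

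The corresponding correlation of log total with log density over all ward-months, the square root of the share, runs from about 0.34 to 0.95. Size dominates only if wards differ more in beds than in antibiotic density.

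**5. What the rest of the model recovers.** Rearranged, log total − log beds − log occupancy = log density + log days. With a fixed effect for each ward (stable bed number) and log occupancy in the model, log total would carry the same information as log density, apart from month length. The protocol specifies neither the log scale nor fixed ward effects. With an untransformed total, an occupancy rate and a random unit effect, the recovery is only partial, and the single antibiotic coefficient still blends between-ward and within-ward contrasts.

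**The case against.** The strongest reply is that the arm comparison is largely protected. The protocol has "one half of the wards will start phase (2) for the first 5 months and then phase (3) for the following 5 months", while the others follow the reverse order, so each ward is seen in both arms and a stable bed number cannot differ between arms within a ward. Occupancy has its own term, which removes much of that component, and the model has a unit level. In a simulation with assumed inputs (13 crossed-over wards, 10 to 30 beds, prescribing unrelated to arm, true rate ratio 0.5), the raw total correlated 0.94 with true density once ward and occupancy were accounted for. At the lower of the simulated incidences and without ward terms, the mean log rate ratio was −0.714 with the total and −0.713 with density. This argument stands for the intervention effect, with one limit: the simulation does not cover prescribing that shifts differently between arms.

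A reader might go further and infer that the covariate measures ward size in place of antibiotic exposure, or that the primary rate ratio is biased. The documents support neither. Density is always a factor in the total, nothing in the protocol shows that size dominates, and no bias in the rate ratio has been demonstrated. Nor can the small number of cases be held against the raw total specifically, because the rate would use the same single parameter.

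It can also be said that scaling a covariate is a matter for the statistical analysis plan. That has limited force here: the protocol states a derivation, and the derivation is a total.

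**Conclusion.** The point holds as a fault of specification. The antibiotic covariate is fixed as a volume in a model for a per-patient-day rate, so it is confounded with ward size and occupancy and partly duplicates the occupancy term. The adjustment for antibiotic exposure and the antibiotic coefficient lose accuracy in the primary model and in secondary analysis A.

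How much is lost cannot be fixed from the protocol. The 12% to 90% range over all ward-months, and 50% to 99% within a ward, rest on assumed and independent variation in beds, occupancy and density. No material effect on the intervention rate ratio is shown. This is a minor improvement, worth making because the better definition is clear and costs almost nothing.

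**What to change.** Define antibiotic use as J01 DDD per 1,000 patient-days in the ward and month, and use this definition in both the primary Poisson model and secondary analysis A. The denominator should be the ward's total patient-days in that month. Patient-days at risk would not match, because the DDD total covers consumption by all patients in the ward.

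The cost is one line of wording. Total ward patient-days are already needed for colonisation pressure, and monthly occupancy rests on the same kind of count, so no new data have to be collected. Sample size and trial conduct are unaffected.
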